## 6.7 Self-supportive Care

Patients with COVID-19 should follow the steps as instructed by their healthcare provider (consistent with guidance from the CDC, local ordinances or practices) to care for themselves and to help protect other people in the home and community from potentially getting sick ([CDC 2020](#)).

In order to manage the symptoms associated with COVID-19, over-the-counter cough, cold, and anti-pyretic medications can be used as necessary by patients in accordance with their respective drug facts label or as instructed by their healthcare provider.

The brand name, generic name, dose, and time must be recorded for every usage occasion.

Since this is an out-patient based study, in the event of significant worsening of COVID-19-related symptoms or two sequential pulse oximetry readings of <94%, patients will be instructed to seek medical attention immediately with their treating provider or go to the emergency room. If the PI or study staff are contacted due to significant clinical worsening of COVID-19 symptoms, the patient will be triaged appropriately to the emergency room or to the outpatient treating provider per clinical judgement. The patient will be removed from the study only if hospitalized (refer to [Section 5.5](#)).

Patients will be provided with information consistent with CDC guidance regarding emergency warning signs for COVID-19 ([CDC 2020](#)) instructing them to seek medical attention immediately, if any of the following occur:

- Trouble breathing
- Persistent pain or pressure in the chest
- New confusion or inability to arouse
- Bluish lips or face

A medical provider must be contacted for any other symptoms that are severe or concerning to the patient. Patients will be instructed to call 911 if they have a medical emergency and be instructed to notify the operator that they have, or think they might have, COVID-19.

Patients will be instructed to put on a cloth face covering before medical help arrives.

## **6.8 Dose Reductions and Holds**

In the event of significant worsening of COVID-19 symptoms, severe or intolerable GI symptoms, or other attributable AEs, the KB109 dose may be down-titrated to a lower dose, or temporarily interrupted, after consultation with the Medical Monitor.

KB109 down-titration occurs by reducing the dose in a step-wise fashion. Specifically, a patient's dose can be reduced after evaluation by the PI or designee, and in consultation with the Sponsor's medical monitor or designee from 72 g/day (36 g BID) to 36 g/day (18 g BID) followed by 18 g/day (9 g BID) until the attributable AE resolves or adequate tolerability is achieved.

During the Intake Period, and at the discretion of the PI and in consultation with the Medical Monitor, patients who have down-titrated their KB109 dose may attempt to increase their dose. This up-titration can only occur at the next up-titration period. Patients can also remain at the down titrated dose, for the remainder of the intake period.

If the patient requires down-titration below 18 g/day (9 g/dose BID), then consultation with the Medical Monitor and PI or designee must occur, and the patient may be withdrawn from the study.

## **6.9 Other Study Restrictions**

Female patients of childbearing potential (as defined in accordance hospital policies and procedures at the patient's outpatient clinic visit) must indicate that they will use one highly effective form of birth control from the day of the first SP dose through the study and for 90 days after the last dose of SP.

Pregnancy status at screening for all females of childbearing potential may be collected by patient self-report or urine pregnancy test.

## **6.10 Randomization, Stratification and Blinding**

All patients deemed eligible for the study will be randomized in a 1:1 ratio to SSC + KB109 or SSC alone group using an interactive response technology (IRT) system. Randomization will be stratified by study site/center, age group ( $\geq 18$  to  $< 45$  years,  $\geq 45$  to  $< 65$  years,  $\geq 65$  years), and comorbidity status (Yes, No).

The study is an open-label study; therefore, no blinding is necessary.

## **7 ADVERSE EVENT REPORTING**

### **7.1 Definitions of AEs, Period of Observation and Recording of AEs**

For convenience, standard terms language included in ICH guidance relevant to the conduct of clinical trials are used in this protocol. An example of such a term included in this protocol is “treatment-emergent,” included in ICH E9. Use of this standard term is not intended to connote treatment with a medicinal product administered.

An AE is defined as any untoward medical occurrence in a patient involved in a clinical study administered a SP and that does not necessarily have a causal relationship with the product. An AE can, therefore, be any unfavorable and unintended sign (including a clinically significant abnormal laboratory finding which has worsened from baseline), symptom or disease temporally associated with the use of a product, accidents, whether or not considered related to the product or study-related procedure.

All AEs are collected from the time the informed consent is signed until the end of the Follow-up Period. This includes events occurring during the Screening Period of the study, regardless of whether or not SP is administered. Where possible, a diagnosis rather than a list of symptoms should be recorded. If a diagnosis has not been made, then each sign or symptom should be listed individually. All AEs should be captured on the appropriate AE pages in the eCRF and in source documents.

All AEs must be followed to closure (the patient’s health has returned to his/her baseline status or all variables have returned to normal), regardless of whether the patient is still participating in the study. Closure indicates that an outcome is reached, stabilization achieved (the PI does not expect any further improvement or worsening of the event), or the event is otherwise explained. When appropriate, medical tests and examinations are performed so that resolution of event(s) can be documented.

## 7.2 AE Assessments

### 7.2.1 Severity

The severity of AEs must be recorded, including the start and stop dates for each change in severity. An event that changes in severity should be captured as a new event. After initiation of KB109, worsening of events that started prior to initiating intake of KB109 must be recorded as new AEs (for example, if a patient experiences mild intermittent dyspepsia prior to dosing of KB109, but the dyspepsia becomes severe and more frequent after first dose of KB109 has been administered, a new AE of severe dyspepsia [with the appropriate date of onset] is recorded in the eCRF).

The medical assessment of severity is determined by using the following definitions:

- Mild:** A type of AE that is usually transient and may require only minimal treatment or therapeutic intervention. The event does not generally interfere with usual activities of daily living.
- Moderate:** A type of AE that is usually alleviated with specific therapeutic intervention. The event interferes with usual activities of daily living, causing discomfort but poses no significant or permanent risk of harm to the research patient.
- Severe:** A type of AE that interrupts usual activities of daily living, or significantly affects clinical status, or may require intensive therapeutic intervention.

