## 3.2 Study Endpoints

### 3.2.1 Primary Endpoint

The primary endpoint is number of patients experiencing study product (SP)-related treatment-emergent adverse events (TEAEs).

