### 8.4.3 Analysis of Endpoints of Interest

#### Adverse Events (AEs)

The analysis of AEs will be based on the Safety Analysis Set. AEs will be coded using the most recent version of Medical Dictionary for Regulatory Activities (MedDRA).

A TEAE is defined as any AE starts or worsens in severity on or after the first dose of SP is taken for SSC + KB109 group or on or after the randomization for SSC group. Adverse event summary tables will include all TEAEs, SP-related TEAEs, SAEs, TEAEs by severity, and TEAEs leading to product discontinuation. Summaries will be presented by MedDRA system organ class and preferred term using frequency counts and percentages by group and overall.

The analysis of the following endpoints will be based on the Full Analysis Set unless otherwise specified.

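### Section 7.2.1 opens a new AE record for any change in severity, so under Section 8.4.3 an AE that began before dosing and only improves afterwards is counted as a TEAE

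*Protocol*

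**What the plan says.** Three parts of the protocol bear on this.

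- **Collection window (Section 7.1).** "All AEs are collected from the time the informed consent is signed until the end of the Follow-up Period". Events that arise in Screening are therefore on file before any product is taken.
- **Recording rule (Section 7.2.1).** "The severity of AEs must be recorded, including the start and stop dates for each change in severity", followed at once by "An event that changes in severity should be captured as a new event". A further sentence then says that, once KB109 has been started, "worsening of events that started prior to initiating intake of KB109 must be recorded as new AEs". Its example is a dyspepsia that goes from mild to severe.
- **TEAE definition (Section 8.4.3, Adverse Events).** A TEAE is "any AE starts or worsens in severity on or after the first dose of SP is taken for SSC + KB109 group" or, in the control arm, "on or after the randomization for SSC group".

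The TEAE flag feeds the tables of all TEAEs, product-related TEAEs and TEAEs by severity. Through the product-related TEAEs it also feeds the primary endpoint in Section 3.2.1.

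**The concern.** The recording rule is triggered by any change in severity, while the analysis definition is meant to pick up onset or worsening. Because each change is dated and entered as a new event, a decrease in severity produces a record whose start date is the day of improvement. If that day falls after first dose or randomization, the record satisfies the first limb of the TEAE definition. An improvement in a pre-existing event is then reported as a newly emerging adverse event.

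Safety is the primary objective. Tables that label improving, pre-existing events as treatment-emergent misdescribe the safety profile of the product and of the comparison arm. Section 7.2.1 is an instruction to sites, so it fixes what is entered in the eCRF. An analyst can repair the flag later only if the new record can be traced to the event it came from, and the protocol requires no such link.

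**Working it through.** No arithmetic applies: the protocol gives no figure for how often an AE is ongoing at first dose or how often it eases afterwards. The check is to apply the recording rule and then the TEAE definition to simple courses of a non-COVID AE in a patient assigned to SSC + KB109.

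| Course of the event | Records under Section 7.2.1 | TEAE under Section 8.4.3, read literally | TEAE as evidently intended |
|---|---|---|---|
| Moderate in Screening, unchanged after first dose | One, with a pre-dose start | No | No |
| Moderate in Screening, severe from Day 3 | New severe record starting Day 3 | Yes | Yes |
| Moderate in Screening, gone on Day 3 | Existing record is closed, no new one | No | No |
| Moderate in Screening, mild from Day 3 | New mild record starting Day 3 | **Yes** | **No** |
| First appears on Day 3 | One, starting Day 3 | Yes | Yes |

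Only the fourth course goes wrong, and it does so in four steps:

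1. The event is collected, because collection runs from consent.
2. Moderate to mild is a change in severity, so a new event is captured, with its own start date.
3. That start date is after first dose, so the limb of the definition concerning AEs that start after dosing is met. The limb concerning worsening is not met.
4. Nothing in Sections 7.1, 7.2.1 or 8.4.3 ties the new record to the earlier one or exempts a decrease.

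The same steps apply in the SSC arm with randomization as the reference point. The two reference points are not the same day. Under Section 4.1 the kit is shipped overnight after randomization and Day 1 is the morning after receipt. An improvement in that gap would create a TEAE in the SSC arm but not in the KB109 arm, so the error need not cancel exactly between arms. The documents do not allow that difference to be sized either.

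The intended meaning can be read from the protocol itself. The sentence in 7.2.1 on events that predate KB109 speaks only of worsening. If every change in severity were meant to count as a fresh start, the worsening limb in 8.4.3 would be redundant.

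**The case against.** The best answer is that a harmless reading exists and fits better. If the first limb of the TEAE definition refers to onset of the underlying event, the worsening limb has a job to do and an easing pre-dose event is not treatment-emergent. Whether split severity records are collapsed before flagging is also a derivation rule that a statistical analysis plan could settle, and the dates needed are collected. This shows what was probably meant. It does not remove the problem: a site that follows 7.2.1 must enter a new AE with a post-dose start date, and the protocol does not say that it belongs to an earlier one.

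The objection carries more weight on size, and three stronger readings that a reader might reach are not supported.

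- **That the primary endpoint is materially inflated.** Section 7.3 directs that an event readily explained by the underlying condition, with no plausible temporal or biological link, be called not related. An event that began before any product was taken and then improved would normally fall there. That its later start date would move investigators towards a related judgement is conjecture.
- **That the excess can be given in percentage points and set against Table 4.** The inputs are not in the documents, and Table 4 concerns the rate of product-related TEAEs, whereas the affected rate is mainly that of all TEAEs.
- **That splitting one event into several records inflates the results generally.** The primary endpoint is a number of patients, and no event-rate analysis is specified. A patient who already has a TEAE is not added again to the number with any TEAE.

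The pool of affected events is also narrow. Symptomatic patients must be screened and randomized within 48 hours of a positive test (Section 5.1); the 12-day maximum in Section 4.2 is given for an asymptomatic patient. Existing conditions go to medical history (Section 4.3.2). COVID-19 symptoms within expected fluctuation or progression are not TEAEs (Section 7.3.3). An event that resolves outright creates no new record.

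**Conclusion.** The point holds as a conflict between a recording rule and an analysis definition. Applied as written, Sections 7.2.1 and 8.4.3 flag as treatment-emergent a non-COVID AE that began before first dose (or before randomization in the SSC arm) and afterwards only eased without resolving. The protocol's own wording elsewhere shows that this was not intended.

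The effect falls mainly on the all-TEAE and TEAE-by-severity tables, where it adds patients who have no other TEAE in the row concerned. On the primary endpoint it is likely small, provided that investigators apply the causality guidance of Section 7.3 as written. No numerical size can be given from the documents. The case for correction is that a stated rule gives a wrong flag and is easy to put right, not that it is shown to change a conclusion of the trial.

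**What to change.** In Section 7.2.1, limit the new-event rule to worsening, for example: *An event that worsens in severity is entered as a new event; a decrease in severity is entered as a dated severity change within the same event.* This keeps the requirement for start and stop dates at each severity level.

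In Section 8.4.3, add a sentence for records already entered under the present rule: *A record created by a decrease in severity keeps the onset date of its parent event when treatment-emergent status is assigned.* Once 7.2.1 is corrected, this sentence matters only for those earlier records.

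The cost is one sentence in each section and a matching line in the eCRF completion guideline. Earlier records can be linked to their parent events in programming from the dates already required, with a query where the link is unclear. Patient care does not change.

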### 7.3 Causality

The PI or designee must make the assessment of relationship to SP for each AE. The PI or designee should decide whether, in his or her medical judgment, there is a reasonable possibility that the event may have been caused by the SP. If there is no valid reason for suggesting a relationship, then the AE should be classified as “not related”. Otherwise, if there is any valid reason, even if undetermined or untested, for suspecting a possible cause-and-effect relationship between the SP and the occurrence of the AE, then the AE should be considered “related”. The causality assessment must be documented in the source document.

The following additional guidance may be helpful:

- **Related (definitely, probably, possibly related):** The temporal relationship between the event and the administration of KB109 is compelling and/or follows a known or suspected response pattern to that product, and the event cannot be explained by the patient’s medical condition, other therapies, or accident.
- **Not Related (definitely not, unlikely related):** The event can be readily explained by other factors such as the patient’s underlying medical condition, concomitant

therapy, or accident and no plausible temporal or biologic relationship exists between the SP and the event.

### 7.3.1 Expectedness

An AE will be considered unexpected if the nature, severity, or frequency of the event is not consistent with the risk information described for the study product discussed within this protocol. The study product is characterized as a prebiotic non-digestible carbohydrate, which has the potential to be poorly tolerated due to local GI when taken at higher amounts. Undesirable GI effects can include acid reflux and heartburn, burping, flatulence, colic (spasmodic abdominal pain), borborygmi (flatulence in the bowels), laxation, reduced appetite, abdominal distension or pain, nausea, abdominal rumbling or an increased defecation frequency. At still higher amounts, watery stools and diarrhea can be expected.

### 7.3.2 Outcome Categorization

The outcome of AEs must be recorded during the course of the study in the eCRF. Outcomes are as follows:

- Fatal
- Not recovered/Not resolved
- Recovered/Resolved
- Recovered/Resolved with Sequelae
- Recovering/Resolving
- Unknown

### 7.3.3 Symptoms of the Disease Under Study

COVID-19 related symptoms of the disease under study should not be classified as TEAEs as long as they are within the normal day-to-day fluctuation or expected progression of the disease not including hospitalizations and are part of the clinical data of the disease that is being collected in the study; however, clinically significant worsening of the symptoms should be recorded as a TEAE (or SAE).

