### 3.2.2 Secondary Endpoints

The secondary endpoints are as follows:

- Time to resolution of overall 13 COVID-19 related symptoms which is defined as from Day 1 until the day at which the overall composite score of 13 COVID-19 related symptoms becomes 0 or 1 and remains at 0 or 1 for the rest of the Intake Period and for the Follow-up Period. Overall composite score of 13 COVID-19 related symptoms is the sum of 13 COVID-19 related symptom scores (i.e., cough, chills/repeated shaking with chills, muscle pain, fever, headache, anosmia/ageusia, shortness of breath, sore throat, gastrointestinal disturbance/symptoms, diarrhea, fatigue, nasal congestion, and chest tightness (CDC 2020). Each COVID-19 symptom will be recorded by patients on a scale of 0: Absent, 1: Mild, 2: Moderately severe, 3: Very severe. The overall composite score ranges from 0 (no symptoms) to 39 (very severe)
- Time to resolution of overall 8 cardinal COVID-19 related symptoms which is defined as from Day 1 until the day at which the overall composite score of 8 cardinal COVID-19 related symptoms becomes 0 or 1 and remains at 0 or 1 for the rest of the Intake Period and for the Follow-up Period. Overall composite score of 8 cardinal COVID-19 related symptoms is the sum of 8 cardinal COVID-19 related symptom scores (i.e., cough, chills/repeated shaking with chills, muscle pain, fever, headache, anosmia/ageusia, shortness of breath, and sore throat)
- Proportion of patients with reduction from Baseline (symptom present at Baseline) in each of 13 individual COVID-19 related symptom at EOI and Follow-up
- Proportion of patients with symptom becomes absent (symptom present at Baseline) at EOI and Follow-up for each of 13 individual COVID-19 related symptom
- Change from Baseline to EOI in overall composite score of 13 COVID-19 related symptoms
- Change from Baseline to EOI in overall composite score of 8 cardinal COVID-19 related symptoms
- Time to resolution of fever (defined as from Day 1 until the day at which a patient's daily maximum temperature achieves and remains below 100.4 °F for the rest of the Intake Period and for the Follow-up Period without an antipyretic medication)
- Proportion of patients with oxygen saturation <95% on Day 14 and Day 35

- Proportion of patients with oxygen saturation <98% on Day 14 and Day 35
- Measures collected from the Healthcare Provider Wellness Visits

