##### **4.3.4.1 Patient-assessed COVID-19 Symptom Score**

Symptom severity will be assessed based on how the patient is feeling at the moment. This will be recorded in TrialPace™.

Patients will self-assess the following 8 cardinal symptoms known to be associated with COVID-19 ([CDC 2020](#)):

1. Fever
2. Chills/Repeated shaking with chills
3. Cough
4. Shortness of breath
5. Headache
6. Muscle pain
7. Anosmia/ageusia
8. Sore throat

Additionally, patients will also report on the following 5 symptoms:

1. Gastrointestinal disturbance/symptoms (other than diarrhea as this will be assessed separately)
2. Diarrhea
3. Fatigue
4. Nasal congestion
5. Chest tightness

Patients will be instructed to rate their symptoms on a scale of 0-3 where:

- 0: Absent (no symptoms evident)
- 1: Mild (symptom present but easily tolerated)
- 2: Moderately severe (definite awareness of symptoms; bothersome but tolerable)
- 3: Very severe (hard to tolerate; interferes considerably with daily activity)

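### Gastrointestinal effects expected from KB109 fall under the COVID-19 symptom exclusion and a self-contradictory causality rule, so the primary safety endpoint probably undercounts mild and moderate ones

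*Protocol*

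**What the plan says.** **Endpoint.** Section 3.2.1: "The primary endpoint is number of patients experiencing study product (SP)-related treatment-emergent adverse events (TEAEs". Section 8.4.3 sets the window: "A TEAE is defined as any AE starts or worsens in severity on or after the first dose of SP is taken" in the SSC + KB109 group, and from randomization in the SSC group.

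**Disease symptoms.** Section 4.3.4.1 has patients score "Gastrointestinal disturbance/symptoms (other than diarrhea as this will be assessed separately", with diarrhea as its own item. Section 3.2.2 puts both into the 13-symptom COVID-19 composite: "gastrointestinal disturbance/symptoms, diarrhea, fatigue, nasal congestion, and chest tightness (CDC 2020".

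**Product effects.** Section 7.3.1: "Undesirable GI effects can include acid reflux and heartburn, burping, flatulence, colic (spasmodic abdominal pain", followed by nausea, distension and more frequent defecation among others, and then: "At still higher amounts, watery stools and diarrhea can be expected". Section 2.3 describes the adverse effects of this class as dose-dependent and confined to the gut.

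**Exclusion.** Section 7.3.3: "COVID-19 related symptoms of the disease under study should not be classified as TEAEs as long as they are within the normal day-to-day fluctuation". The sentence also covers expected progression, leaves hospitalizations outside the exclusion, and applies to symptoms collected as disease data. It ends by keeping clinically significant worsening as a TEAE or SAE. The Synopsis (Methodology) repeats the exclusion without that last part. Neither place treats the gastrointestinal items differently.

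**Worsening.** Section 7.2.1 requires that an event which began before KB109 and worsens afterwards be entered as a new AE. Its example is dyspepsia.

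**Causality.** The lead paragraph of Section 7.3 makes an AE related if there is any valid ground, even an untested one, to suspect a link. The guidance below it describes a related event as one with a compelling timing or known response pattern, "and the event cannot be explained by the" patient's medical condition, other treatment or an accident. It describes a not-related event as one that other factors readily explain and for which no plausible link in time or biology exists.

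**The concern.** The harm the protocol expects from KB109 is gastrointestinal, and every participant has an illness whose collected symptoms include gastrointestinal disturbance and diarrhea. An event of this kind must pass two steps to reach the primary endpoint: it must be recorded as a TEAE, and it must be judged related. At the first step, Section 7.3.3 lets the investigator leave it out as a disease symptom. At the second, the guidance in Section 7.3 lets the illness stand as a reason not to call it related. Both steps rest on judgement in an open-label study.

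At stake is the single primary result. The control arm cannot correct it, because relatedness to KB109 is an attribution made for patients who took KB109. Table 4 expresses the precision of the study in terms of this same rate, and its intervals describe sampling error only. A loss through classification would not show in them.

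**Working it through.** **1. The passages applied to one event.** Take a patient on KB109 who reports mild or moderate diarrhea in the intake period.

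- *Diarrhea began before the first dose and is now worse.* Section 7.2.1 requires a new AE. Section 7.3.3 says it is not a TEAE if it lies within the expected course of the disease and is not clinically significant worsening. The two give different answers.
- *Diarrhea is new after the first dose.* The sentence in Section 7.2.1 on events that began before KB109 does not reach it. Section 7.3.3 decides, and sets no threshold for when a symptom has worsened to a clinically significant degree.
- *If recorded, is it related?* Lead paragraph of Section 7.3: yes, since Section 7.3.1 supplies a valid reason to suspect KB109. Description of related: no, since COVID-19 can explain it. Description of not related: also no, since a plausible link to KB109 exists. The event fits neither description.

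The permissive lead paragraph acts only on events already recorded, so it cannot restore what Section 7.3.3 has kept out. That is why the likely direction is downward.

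**2. The plan's own figure.** Table 4 gives 95% intervals for assumed rates of 10%, 20%, 40% and 60% at 148 and 170 evaluable patients per group. Exact (Clopper-Pearson) limits, with the count rounded to whole patients (15, 30, 59, 89 of 148; 17, 34, 68, 102 of 170), reproduce all eight intervals and half-widths to 0.1 point. At 40% they are 31.9% to 48.2% (half-width 8.2) and 32.6% to 47.8% (half-width 7.6).

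**3. What a loss would do.** Let p be the true share of KB109 patients with a product-related TEAE, and f the share of those patients lost from the count. The endpoint counts patients, so a patient is lost only if no other related TEAE is recorded for them. The protocol gives no value for f; the range below is an assumption.

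Observed rate = p(1 − f); bias = p × f.

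| True p | f = 10% | f = 25% | f = 50% | Table 4 half-width (n = 148 / 170) |
|---|---|---|---|---|
| 20% | 18% (−2) | 15% (−5) | 10% (−10) | 6.8 / 6.3 |
| 40% | 36% (−4) | 30% (−10) | 20% (−20) | 8.2 / 7.6 |

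At a true 40% and f = 25%, the observed interval is 22.5% to 37.8% (n = 148) or 23.2% to 37.5% (n = 170). Neither contains 40%.

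The smallest f at which the observed exact interval no longer contains the true rate is:

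| True p | n = 148 | n = 170 |
|---|---|---|
| 10% | about 49% | about 44% |
| 20% | about 34% | about 31% |
| 40% | about 20% | about 18% |
| 60% | about 14% | about 13% |

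**The case against.** A reader might infer that the endpoint misses gastrointestinal effects outright, or that the causality text drives the count towards zero. The protocol does not support that. The exclusion in Section 7.3.3 is conditional, and a product effect is strictly neither fluctuation nor progression of COVID-19. Clinically significant worsening stays a TEAE. Section 7.2.1 already sends worsening of pre-existing symptoms to a new AE, with a gastrointestinal example. The restrictive clause in Section 7.3 is offered only as additional guidance, under a lead paragraph that says the opposite. Sections 4.1 and 6.8 also treat gastrointestinal symptoms as a possible product effect. Several effects listed in Section 7.3.1, such as reflux or burping, are not obviously COVID-19 symptoms, and nothing in the protocol says an investigator would file them as such.

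It is also fair that the data are not lost. Both items are scored daily during intake in both arms, the change in each individual symptom score is an exploratory endpoint (Section 3.2.3), and supportive tables may be left to the SAP (Section 8.4).

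These points limit the claim without removing it. An investigator cannot tell from the outside whether mild diarrhea is disease course or product effect, and that is the case for which the rules disagree. Section 7.2.1 does not resolve the conflict; for pre-existing symptoms it is one side of it. A supportive table cannot repair the definition of the primary endpoint, which the protocol fixes.

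**Conclusion.** The plan is wrong as written on this point. Sections 7.3.3 and 7.2.1 conflict for gastrointestinal symptoms present before dosing, and Section 7.3 contradicts itself for events that both COVID-19 and KB109 could explain. The primary endpoint therefore cannot be applied consistently to the kind of event the protocol most expects from the product. An undercount of mild and moderate events is probable; severe or clinically significant ones are still captured.

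The size cannot be obtained from the protocol. Neither the true rate nor f is given, and the 40% used for illustration is one of four assumed rates in Table 4. If f is 10%, the bias of 2 to 4 points at true rates of 20% to 40% stays inside the planned half-width. If f is 25%, it stays inside at a true 20% (5 points) but exceeds it at 40% (10 points). At 50% it exceeds it at both.

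**What to change.** 1. **Section 7.3.** In the description of a related event, delete the clause beginning "and the event cannot be explained by the", through to its mention of accident, so that the reasonable-possibility rule in the lead paragraph governs.
2. **Section 7.3.3 and the Synopsis (Methodology).** State that the exclusion does not apply to gastrointestinal disturbance or diarrhea that starts or worsens in severity within the TEAE window of Section 8.4.3: from the first dose for SSC + KB109, from randomization for SSC. State that these are recorded as AEs in both arms, in line with Section 7.2.1. Using that window keeps events later on Day 1, after the first dose.
3. **Added table.** By randomized arm, the number and percentage of patients whose diary score for gastrointestinal disturbance or for diarrhea rises by at least 1 during intake from the Day 1 value (pre-dose in the KB109 arm). This needs no attribution and no new data, and it serves the stated objective of comparing safety with SSC alone.

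The cost is a change to protocol and eCRF guideline wording and one further table. There will be more AE entries, some of which reflect ordinary COVID-19 fluctuation, and the reported AE rate will be less favourable. Some illness-caused events may also be called related; the by-arm table helps to put these in proportion.
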